### Participant timeline {13}

Subjects in the Death Café arm of the study will participate in 4 debriefing sessions over 3 months from the time of enrollment. Surveys will be administered by email to participants in both arms of the study prior to the intervention, at 1 month, at 3 months, and at 6 months after enrollment. Figures 1 and 2 demonstrate the flow of participants through the study.

**Fig. 1 Fig1:**
[figure not shown]
STOPTHEBURN flow diagram

**Fig. 2 Fig2:**
[figure not shown]
SPIRIT diagram depicting the timeline of the STOPTHEBURN study

### Sample size {14}

The target enrollment is 200 ICU employees, of which we expect approximately 100 physicians and 100 non-physicians (nurses and therapists) in the study. This is based on a power analysis we performed for the ability to detect 20% reduction in burnout prevalence or a change of greater than 4 in mean Maslach Burnout Inventory Score (power of 0.8, alpha of 0.05).

### Recruitment {15}

Recruitment will be performed in person at each ICU site and electronically via email to employee listservs on a biweekly basis until target enrollment is reached. Recruitment will involve screening for eligibility, providing potential participants with information about the study, and obtaining informed consent. Participants will be offered compensation for completion of a minimum number of study procedures. This will be $140 for completion of the Death Café study arm and $40 for the control arm.

## Data collection and management

### Plans for assessment and collection of outcomes {18a}

Relevant information related to the outcome measures is noted under the outcomes section. Data will be collected via surveys generated using Research Electronic Data Capture (REDCap) software, which is a secure online system [44]. Participants will enter their own data online.

### Plans to promote participant retention and complete follow-up {18b}

Participants will be reminded of Death Café debriefing sessions by study investigators on a weekly basis and will receive notifications and reminders for surveys through REDCap. Any participant who fails to complete one or more study surveys or Death Café debriefing sessions will still be invited to complete scheduled follow-up surveys up to the final time point.

Monetary compensation will also be provided for completion of a minimum number of study procedures as follows. For the Death Café intervention arm, participants completing all four surveys and at least 4 Death Café debriefing sessions will receive $140. For the control arm, participants completing all four surveys will receive $40.

### Data management {19}

Data will be collected and stored in REDCap on the Tulane University server. The trial investigators and statistician will have access to the final dataset. All data will be password-protected, and the REDCap database has multiple mechanisms in place to ensure data integrity. Additional data management procedures can be provided by the study investigators upon request.

### Confidentiality {27}

The risk of loss of privacy will be minimized by labeling survey responses and data with only an alphanumerical code (the first three letters of the subject’s mother’s maiden name and the last three digits of their phone number) instead of the participant’s name. The surveys will be sent through REDCap survey software. Names and contact information will be used to generate a list of those enrolled in the study, to send participants surveys, and to let those in the intervention arm know the dates and times of Death Café sessions.

The researchers will discuss the need for keeping the proceedings confidential with the Death Café groups at the beginning and end of each session. This will serve to protect both the subjects participating in the Death Café as well as any patients whose cases are discussed.

The research team will keep the survey responses in the REDCap secure online database. The aggregate data from the surveys will be stored in REDCap and in a passkey-protected folder on a password-protected laptop that only the research team can access. Paper documents such as consent forms will be kept in a locked filing cabinet in the faculty advisor’s locked office. Results of the study will be presented in aggregate with no inclusion of names or identifying information. The raw survey responses and consent forms will be kept up to 1 year after duration of the study and then destroyed.

### Plans for collection, laboratory evaluation, and storage of biological specimens for genetic or molecular analysis in this trial/future use {33}

No biological specimens will be collected as a part of this trial.

## Statistical methods

### Statistical methods for primary and secondary outcomes {20a}

Descriptive statistics will be reported for participant recruitment, study dropout, and engagement with the intervention. Baseline characteristics for each group will be reported. All analyses will be conducted on an intention-to-treat basis.

Unadjusted associations between independent risk factors (i.e., age, gender, and presence of primary or secondary outcome) will be assessed using Student’s *t* test or Wilcoxon rank sum test for continuous variables and a chi-square test for categorical variables. These risk factors and scores will be compared between the intervention and control group as well as analyzed from the beginning to the end of the intervention period (pre-survey compared to 3-month and 6-month scores). Mixed model regression will also be utilized to analyze differences between groups. Qualitative thematic analysis of free text response feedback regarding the intervention will be performed. All analyses will be performed using SAS Enterprise Guide 5.1 (SAS Institute, Inc., Cary, NC).

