## Assignment of interventions: allocation

### Sequence generation {16a}

Randomization will utilize an online random number generator and will be performed in pairs such that each time a physician is randomized to a study arm, a non-physician will also be randomized to that study arm for balance.

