### Challenges

While we aim to recruit a sample which represents all ICU employees, participants with burnout, depression, and anxiety symptoms may be difficult to engage in a research study. Feeling already overwhelmed, the employees most at risk may not engage with a time-consuming intervention, which could lead to underestimation of the intervention’s effect. We will do our best to increase subject participation by making participation in the study as convenient as possible using virtual platforms and by providing monetary reimbursement for the time participants spend completing surveys and participating in Death Café sessions.

We recognize that our intervention may have differential impact based on a number of factors. It is possible that burnout may vary at different times of the year with busier times leading to higher rates of burnout. The COVID-19 pandemic may increase the level of burnout and also limit the availability of those most in need to seek help. Certain demographic factors (marital status, having children, etc.), factors related to personal wellness (sleep, history of depression or anxiety, etc.), and those related to work environment (recent conflicts or deaths, etc.) may also play a role. We will not specifically recruit participants based on these factors, as our randomized controlled trial structure will help to account for these and other potential confounders. We will be performing multivariate regression analyses and other subgroup analyses to help us to evaluate these relationships. We hope to identify the employee subpopulations who benefit the most from Death Café debriefing sessions.

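### Section {20a} names no paired method for the pre-to-post comparison and does not say whether the unadjusted tests or the mixed model lead the between-arm analysis

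*Protocol article*

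**What the plan says.** All of this is in the Protocol article. Section {20a} sets out the methods in three consecutive sentences.

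- The first concerns unadjusted associations with risk factors, among which it counts the outcomes themselves. For these it lists "Wilcoxon rank sum test for continuous variables and a chi-square test for categorical variables", with Student's t as the alternative to the rank-sum test. It does not say whether the t test is paired or independent. It names no signed rank or McNemar test.
- The second says what will be compared: "These risk factors and scores will be compared between the intervention and control group as well as analyzed from the beginning to the end". A bracket then gives the time points: "pre-survey compared to 3-month and 6-month scores".
- The third reads: "Mixed model regression will also be utilized to analyze differences between groups".

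Outcomes {12} has the MBI, PHQ-8 and GAD-7 completed by the same participants at enrolment, 1, 3 and 6 months. The MBI is reported both as mean scores and as burnout yes/no. Sequence generation {16a} builds professional role into the allocation: "each time a physician is randomized to a study arm, a non-physician will also be randomized to that study arm for balance". The Challenges section says of burnout: "It is possible that burnout may vary at different times of the year". It adds that COVID-19 may raise it.

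**The concern.** Two comparisons of different kinds share one list of tests.

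The comparison of baseline with 3 and 6 months is within person. Rank-sum and chi-square tests treat the two sets of scores as if they came from different people, so they ignore the correlation between a person's own scores and use the wrong standard error. The third sentence does not repair this, because it assigns the mixed model to differences between groups only.

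The within-person comparison also has no control. Enrolment is planned from July 2020 to July 2021 (Trial status). By the article's own account, burnout may move over that time with season and the pandemic, so change within an arm mixes those movements with any effect of the sessions.

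The between-arm comparison is the randomised one. Here the text gives two analyses of the same outcomes, an unadjusted test and a mixed model, without ranking them. If the unadjusted test leads, the baseline MBI score is collected but adds nothing to precision. If the mixed model leads, the reader cannot tell whether it uses that score.

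**Working it through.** **Inputs from the Protocol article.** Total sample 200 (Sample size {14}) and 1:1 allocation (Trial design {8}), so 100 per arm. Target effect: a 20% fall in burnout prevalence or a change above 4 points in mean MBI; power 0.8, alpha 0.05 ({14}). Background burnout prevalence: as high as 60% (Background and rationale {6a}).

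**Assumptions.** The article gives no correlation r between baseline and follow-up, so 0.3, 0.5 and 0.7 are shown. It gives no SD, so one is solved for below. Tests are two-sided and there is no dropout.

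**1. The plan's own figure.** Reading the 20% as absolute, from 60% to 40%:

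n per arm = [1.96·√(2·0.5·0.5) + 0.8416·√(0.6·0.4 + 0.4·0.6)]² / 0.20² = (1.386 + 0.583)² / 0.04 ≈ 97, or 194 in total. This is within 3% of 200.

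For the 4-point effect, 80% power at 100 per arm needs SD = 4·√50 / (1.96 + 0.8416) = 10.1. The sample size does not decide this point, but it supplies the SD used in step 3.

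**2. Pre-to-post comparison within one arm.** For n people with common SD s:

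- paired SE = s·√(2(1 − r)/n)
- independent-sample SE = s·√(2/n)
- ratio = 1/√(1 − r)

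The true type I error of the independent-sample test at nominal 0.05 is 2·[1 − Φ(1.96/√(1 − r))]. A simulation (4,000 replicates, 100 pairs, normal scores) checks this. It also gives power for a true shift of 4/10.1 = 0.396 SD.

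| r | SE ratio | Type I error, formula | Simulated: independent t | Simulated: rank sum | Simulated: paired t | Power, independent t | Power, paired t |
|---|---|---|---|---|---|---|---|
| 0.3 | 1.20 | 0.019 | 0.021 | 0.020 | 0.054 | 0.84 | 0.91 |
| 0.5 | 1.41 | 0.006 | 0.007 | 0.008 | 0.053 | 0.88 | 0.98 |
| 0.7 | 1.83 | 0.0003 | 0.0005 | 0.0005 | 0.056 | 0.93 | 0.9995 |

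The rank-sum test behaves like the independent t test. For burnout yes/no with similar proportions before and after, the same ratio holds, with r as the correlation of the two yes/no values.

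**3. Between arms.** Using baseline as a covariate reduces the residual SD to 10.1·√(1 − r²). Power = Φ(4 / (SD·√(2/100)) − 1.96).

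| Analysis | SD used | Power at 100 per arm | Total N for 80% power |
|---|---|---|---|
| Unadjusted | 10.1 | 0.80 | 202 |
| Baseline-adjusted, r = 0.3 | 9.63 | 0.835 | 184 |
| Baseline-adjusted, r = 0.5 | 8.75 | 0.899 | 152 |
| Baseline-adjusted, r = 0.7 | 7.21 | 0.975 | 104 |

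The unadjusted between-arm test has no standard-error fault from leaving baseline out. It only has less power.

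**The case against.** The strongest reply is that a suitable method is already planned. A mixed model handles repeated scores and can carry the baseline MBI. Section {20c} relies on it for missing data, {20b} uses it for subgroups by role, and the Challenges section plans multivariate regression. A reader might infer that the plan as a whole throws the baseline away. The documents do not support that: nothing says the mixed model omits baseline. Detail of that model may also sit in an analysis plan that is not shown, so its absence here is no fault in itself.

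The link between the listed tests and the pre-to-post comparison is also an inference. The second sentence of {20a} names no test of its own, and the t test could be run paired. Both points stand as far as they go. But the second sentence refers straight back to the first, the third is confined to between-group differences, and rank-sum and two-sample chi-square tests have no paired form.

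Two further inferences are tempting and should be resisted.

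- A reader might expect the wrong standard error to produce false positives. With positive correlation it does the opposite, as the table shows.
- A reader might add that participants sharing sessions breaks independence in the intervention arm. The article describes biweekly sessions of which participants attend at least four. It describes no fixed groups and gives no group size or intraclass correlation, so no such error can be shown from it.

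Finally, the hypothesis in Objectives {7} and the comparator section {6b} are framed as intervention against control. There is no evidence that the investigators mean to present within-arm change as the effect. The recommendation below only makes that explicit.

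**Conclusion.** The point holds in a limited form.

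As written, {20a} leaves the within-person comparison with tests of which two, rank sum and chi-square, assume independent samples. The consequence is a standard error 1.20 to 1.83 times too large for assumed correlations of 0.3 to 0.7, and hence a test that is too conservative and can miss real change. This rests on the natural reading of the section, which is not spelled out. The within-arm result would not be a randomised comparison even with the right test.

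The unadjusted between-arm tests are valid. If they lead, the cost is power: 0.80 against 0.835, 0.899 and 0.975 at correlations of 0.3, 0.5 and 0.7, assuming an SD near 10.1 and 100 per arm with no dropout. At the low end the gain is small. If the mixed model leads and already uses baseline, that cost disappears. The section does not settle either question.

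**What to change.** Reword {20a} as follows.

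- Name the mixed model, adjusted for baseline score and for role (physician or non-physician, as used in the randomisation), as the primary between-arm analysis.
- Limit the t, rank-sum and chi-square tests of outcomes to description.
- For any within-arm change, use paired methods: paired t or signed rank for scores, McNemar for the yes/no outcomes. State that no conclusion on efficacy will be drawn from it.

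This costs the wording of one section. Baseline scores and role are already collected, and the planned SAS software fits these models. It should be settled before the data are analysed.

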**Methods:**

A randomized controlled trial will be conducted in two large academic medical centers. Two hundred ICU clinicians will be recruited with target enrollment of 100 physicians and 100 non-physicians (nurses, pharmacists, therapists). Participants must have worked in the ICU for the equivalent of at least 1 full time work week in the preceding 4 weeks. Enrolled subjects will be randomized to virtually attend biweekly debriefing sessions facilitated by a psychotherapist for 3 months or to a control arm without sessions. Our debriefs are modeled after Death Cafés, which are informal discussions focusing on death, dying, loss, grief, and illness. These sessions allow for reflection on distressing events and offer community and collaboration among hospital employees outside of work.

The primary outcome is clinician burnout as measured by the Maslach Burnout Inventory (MBI) Score. Secondary outcomes include depression and anxiety, as measured by the Patient Health Questionnaire 8 (PHQ-8) and Generalized Anxiety Disorder 7-item scale (GAD-7), respectively. Questionnaires will be administered prior to the intervention, at 1 month, at 3 months, and at 6 months after enrollment. These values will be compared between groups temporally. Qualitative feedback will also be collected and analyzed.

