### Trial design {8}

STOPTHEBURN is a parallel group randomized controlled trial with a 1:1 allocation ratio.

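### The article names unadjusted tests and an unspecified mixed model for the arm comparison, and does not commit to using the baseline score; adjusting for it would add precision at no cost

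*Protocol article*

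**What the plan says.** The abstract sets the measurement schedule: "Questionnaires will be administered prior to the intervention, at 1 month, at 3 months, and at 6 months after enrollment". The participant timeline repeats it for both arms, so a baseline score on each scale is planned for everyone.

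Section {20a} first describes unadjusted associations for age, gender and presence of an outcome, tested by Student's t, Wilcoxon rank sum or chi-square. It continues: "These risk factors and scores will be compared between the intervention and control group", and adds that scores will be followed from the pre-survey to 3 and 6 months. Then comes: "Mixed model regression will also be utilized to analyze differences between groups". No covariates, time structure or baseline handling are given for that model, and no analysis is called primary.

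Other sections also refer to regression. Section {20b} uses mixed models for subgroups, {20c} relies on the mixed model for missing data, and the Challenges section plans multivariate regression on demographic, wellness and work factors. None of them names the baseline MBI, PHQ-8 or GAD-7 score as a term in the arm comparison.

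The sample size section aims to "detect 20% reduction in burnout prevalence or a change of greater than 4 in mean Maslach Burnout Inventory Score" with "power of 0.8, alpha of 0.05". It gives no SD and no correlation.

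**The concern.** Burnout, depression and anxiety scores can be expected to differ between people and to persist within them. An arm comparison that ignores the baseline score carries all of that between-person spread in its standard error. Adjusting for the baseline removes the part it predicts and leaves the target difference in means unchanged.

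The baseline is already to be collected, so the gain is free. It matters here because 200 participants leave little margin: the calculation below needs almost all of them, and the sample size section mentions no allowance for non-response. As written, a reader cannot tell whether the reported arm effect will come from a t test, a change comparison or a baseline-adjusted model, and these differ in precision.

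**Working it through.** **Inputs from the article.** "The target enrollment is 200 ICU employees"; a "parallel group randomized controlled trial with a 1:1 allocation ratio", hence about 100 per arm; alpha 0.05 and power 0.80; target difference 4 points.

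**Assumptions.** Two-sided alpha (sidedness is not stated). Control burnout rate 60%, taken from the background section. SD back-solved. Baseline-to-follow-up correlation ρ of 0.3, 0.5 or 0.7. The article does not say whether the 4 points refer to the total MBI score or a subscore.

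**Step 1: the plan's own figure.** Reading the 20% as absolute, 60% versus 40%, without continuity correction:

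n per arm = [1.960·√(2·0.5·0.5) + 0.842·√(0.6·0.4 + 0.4·0.6)]² / 0.20² ≈ 97, total 194.

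This is close to 200. A relative reduction (60% to 48%) would need 270 per arm, 540 in total, so the absolute reading is the one that fits.

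**Step 2: the SD implied by 4 points.**

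SD = 4 / [(1.960 + 0.842)·√(2/100)] = 4 / 0.396 ≈ 10.1.

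**Step 3: precision and power at 100 per arm.** SE = s·√(2/100) and power = Φ(4/SE − 1.960), where s is:

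- unadjusted: 10.1
- baseline-adjusted: 10.1·√(1 − ρ²)
- change from baseline: 10.1·√(2(1 − ρ))

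Unadjusted: SE = 1.43, power = Φ(2.80 − 1.96) = 0.80, at every ρ.

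| ρ | Adjusted SE | Adjusted power | Variance saved | n per arm for 0.80, adjusted | Change-score power |
|---|---|---|---|---|---|
| 0.3 | 1.36 | 0.835 | 9% | 92 | 0.658 |
| 0.5 | 1.24 | 0.899 | 25% | 76 | 0.800 |
| 0.7 | 1.02 | 0.975 | 49% | 52 | 0.951 |

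**Step 4: what the unspecified mixed model would deliver.** If the pre-survey is a response with its own mean in each arm, then with complete data the arm-by-time contrast against baseline is the difference in mean change, which is the last column. That beats the unadjusted test only when ρ exceeds 0.5 and is worse below it. If baseline means are constrained equal across arms, precision is about that of the adjusted column. The article does not say which form is meant.

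**Step 5: sensitivity to the SD.**

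| SD | Unadjusted power | Adjusted power, ρ = 0.3 / 0.5 / 0.7 |
|---|---|---|
| 10.1 | 0.80 | 0.84 / 0.90 / 0.98 |
| 12 | 0.65 | 0.70 / 0.78 / 0.91 |
| 15 | 0.47 | 0.51 / 0.59 / 0.75 |

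The direction holds throughout; the size depends on both assumed quantities.

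**Step 6: bias.** In 4,000 simulated trials at each ρ with a true effect of −4, all three estimators averaged about −4.0. Their empirical SDs at ρ = 0.5 were 1.44 unadjusted, 1.43 change and 1.26 adjusted, in line with the formulas.

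**The case against.** The strongest reply is that {20a} attaches the word unadjusted and the three tests to risk-factor associations. The sentence on comparing scores between arms names no test, and the method named for between-group differences is the mixed model, on which {20c} also relies. This stands in part. A reader might infer that every between-arm comparison is unadjusted and that the trial therefore throws its baseline away. The text does not support that: a mixed model is planned for the same differences, and the pre-survey enters the comparison with 3 and 6 months. Loss of precision is certain only for the simple tests.

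A second reply is that covariates and baseline handling belong in an analysis plan or full protocol that is not shown. This also has force and lowers confidence. It is not a complete answer, because the article itself names unadjusted tests, adds the mixed model alongside them and ranks neither.

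A third is that nothing planned is invalid. That is correct. A reader might also infer that chance baseline differences bias the unadjusted estimate, or cost something beyond the lost power. Neither follows. At ρ = 0.5, one SD of baseline imbalance is 1.43 points and carries 0.71 into the estimate. The unadjusted variance, 1.43² ≈ 2.04, is 0.71² + 1.24² ≈ 0.51 + 1.53. The imbalance is already inside the unadjusted standard error, so it must not be counted twice, and over repeated randomizations it averages to zero.

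**Conclusion.** The article leaves the between-arm analysis open between valid but less precise tests and a mixed model whose use of the baseline is unstated. Baseline adjustment would raise power from about 0.80 to between 0.84 and 0.98 over correlations of 0.3 to 0.7; at the low end the gain is only 3.5 percentage points. These figures assume 100 analysed per arm, a 4-point difference and an SD of about 10, and neither the SD nor the correlation is in the document. The gain for the binary outcomes is not quantified here.

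This is a free improvement, not an error in the plan. Confidence is moderate, because the model may be specified in a document not shown.

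**What to change.** In section {20a}:

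- Name the mixed model as the primary between-arm analysis of each MBI score, PHQ-8 and GAD-7.
- Include the same scale's pre-intervention score as covariate, or constrain baseline means to be equal across arms, with arm-by-visit terms. The constrained form also keeps participants who lack a baseline score.
- Read the arm difference at the stated follow-up visit.
- For the binary outcomes (burnout, and PHQ-8 or GAD-7 of 10 or more), include the baseline score in the model and report an adjusted risk difference.
- Keep the t, Wilcoxon and chi-square comparisons as supportive.

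The cost is a few sentences, settled before outcome data are examined. It needs no new data, visits or participants. If an analysis plan already says this, the article's wording need only be aligned with it.
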